**CLINICAL DATA**

4. CID: | | | | | , (9) NA

1. Weight (kg):
2. Height (m):

**UC CLINICAL ACTIVITY: LICHTIGER INDEX (LI)**

**INSTRUCTIONS**: Circle one answer for each symptom and the equivalent score.

| **SYMPTOMS** | **SCORE** |
| --- | --- |
| **Diarrhea (number of daily bowel movements)**  0-2  3 or 4  5 or 6  7 to 9  10 | 0  1  2  3  4 |
| **Nocturnal diarrhea**  No Yes | 0  1 |
| **Visible bleeding in stool (% of movements)**  0  <50  >50  100 | 0  1  2  3 |
| **Fecal incontinence**  No Yes | 0  1 |
| **Abdominal pain or cramps**  None Light Moderate  Severe | 0  1  2  3 |
| **General well being**  Perfect Very good Good Regular Bad  Terrible | 0  1  2  3  4  5 |
| **Abdominal tenderness**  None  Light and localized | 0  1 |

| Light to moderate and diffuse  Severe or rebound | 2  3 |
| --- | --- |
| **Need for antidiarrheal drugs**  No Yes | 0  1 |

1. Scores sum from the previous table:
2. Classify clinical activity according to total score:
   1. Remission (<4)
   2. Light/moderate activity (5-10)
   3. Severe colitis (>10)

(9) NA

PHARMACOTHERAPEUTIC DATA

1. In use for oral sulfassalazine 500mg: (1) yes (2) no (9) NA if yes, dose/day:
2. In use for oral mesalamine 400mg: (1) yes (2) no (9) NA if yes, dose/day:
3. In use for oral mesalamine 500mg: (1) yes (2) no (9) NA if yes, dose/day:
4. In use for oral mesalamine 800mg: (1) yes (2) no (9) NA if yes, dose/day:
5. In use for rectal mesalamine 250mg: (1) yes (2) no (9) NA if yes, dose/day:
6. In use for azathioprine 50mg:(1) yes (2) no (9) NA if yes, dose/day:
7. In use for oral cyclosporine 25mg: (1) yes (2) no (9) NA if yes, dose/day:
8. In use for oral cyclosporine 50mg: (1) yes (2) no (9) NA if yes, dose/day:
9. In use for oral cyclosporine 100mg: (1) yes (2) no (9) NA if yes, dose/day:
10. In use for oral cyclosporine 100mg/mL: (1) sim (2) no (9) NA if yes, dose/day:
11. Using medication for other conditions? (1) yes (2) no (9) NA if yes, answer items n° 20 and 21.
12. List medications currently in use for other diseases:

| MEDICATION  (generic name) | CONCENTRATIO N | PHARMACEUTI CAL FORM | ADMINISTRATIO N ROUTE | INDICATIO N | ATC CODE  (Level 5) | ATC CODE  (Level 3) |
| --- | --- | --- | --- | --- | --- | --- |
|  |  |  |  |  |  |  |
|  |  |  |  |  |  |  |
|  |  |  |  |  |  |  |
|  |  |  |  |  |  |  |
|  |  |  |  |  |  |  |
|  |  |  |  |  |  |  |

1. Observations:

#### Appendice 4 – Survey Questionnaire for final data collection

1. Participant identification code: | | | | |
2. Date (time 0): / /
3. Interviewer:

**QUALITY OF LIFE DATA (BRASIL SF 36)**

**Instructions**: this survey asks you about your health. This information will keep us informed of how you feel and how well you are able to carry out your activities of daily living. Answer each question by marking the answer as indicated. If you are unsure how to respond, please try to answer as best you can.

[figure not shown]

[figure not shown]

[figure not shown]

[figure not shown]

[figure not shown]

**ADHERENCE DATA: MORISKY-GREEN-LEVINE TEST (MGLT)**

### **Instructions**: mark below with an “X” according to the treatment for UC

|  |  | **YES** | **NO** |
| --- | --- | --- | --- |
| **NON INTENTIONAL** | 1. Do you ever forget to talke your medicine? |  |  |
|  | 2. Are you careless at times about taking your medicine? |  |  |
| **INTENTIONAL** | 3. When you feel better do you sometimes stop taking your medicine? |  |  |
|  | 4. Sometimes if you feel worse when you take the medicine, do you stop taking it? |  |  |

1. According to MGLT, classify:
2. Adherent, if answered NO to ALL questions
3. Moderate adherence, if answered YES to 1 or 2 questions
4. Low adherence, if answered YES to 3 or 4 questions

(9) NA

1. Non-adherence tipology according to MGLT: (1) Intentional (2) Non-intentional (3) Both (9) NA

**CLINICAL DATA**

1. Weight (kg):

**UC CLINICAL ACTIVITY: LICHTIGER INDEX (LI)**

**INSTRUCTIONS**: Circle one answer for each symptom and the equivalent score.

| **SYMPTOMS** | **SCORE** |
| --- | --- |
| **Diarrhea (number of daily bowel movements)**  0-2  3 or 4  5 or 6  7 to 9  10 | 0  1  2  3  4 |
| **Nocturnal diarrhea**  No Yes | 0  1 |
| **Visible bleeding in stool (% of movements)**  0  <50  >50  100 | 0  1  2  3 |
| **Fecal incontinence**  No Yes | 0  1 |
| **Abdominal pain or cramps**  None Light Moderate  Severe | 0  1  2  3 |
| **General well being**  Perfect Very good Good Regular Bad  Terrible | 0  1  2  3  4  5 |
| **Abdominal tenderness**  None  Light and localized  Light to moderate and diffuse Severe or rebound | 0  1  2  3 |

| **Need for antidiarrheal drugs**  No Yes | 0  1 |
| --- | --- |

1. Scores sum from the previous table:
2. Classify clinical activity according to total score:
   1. Remission (<4)
   2. Light/moderate activity (5-10)
   3. Severe colitis (>10)

(9) NA

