#### Data Categorization

Socio-demographic and economic variables will be analyzed:

- - sex, age, ethnicity/color, origin, marital status, monthly income, education.

Pharmacotherapeutic variables will be analyzed:

- - prescription drugs classified according to the Anatomical Therapeutic Chemical Classification (ATC)[12] for UC and comorbidities, at levels 3 and

5. This variable will be collected at Time 0 and if there is a change in treatment;

- - therapeutic regimens for UC. This variable will be collected at Time 0 and if there are changes in treatment;
  - self-reported drug non-adherence for drugs being treated for UC, according to MGLT[8]. This variable will be collected at Time 0 and 6 months;
  - number of educational interventions of the “Drug Guidance” type: frequency of guidance per drug per patient carried out during the intervention program;
  - number of behavioral interventions of the “Therapeutic Scheme” type: frequency of therapeutic schemes per patient performed during the intervention program;
  - number of behavioral interventions of the “Pharmaceutical Guidance Table” type: frequency of the table per therapeutic regimen per patient, performed during the intervention program;
  - number of behavioral interventions of the type “SMS Reminder Type”: frequency of SMS reminder type per patient, performed during the duration of the intervention program;

Clinical variables will be analyzed:

- - disease activity - Lichtiger index[9], which establishes the clinical status of UC. This variable will be collected at Time 0 and 6 months;

Subjective variables reported by the patient will be analyzed (Patient Reported Outcomes - PRO):

- - quality of life. This variable will be collected at Time 0 and 6 months using the Brazil SF-36 questionnaire[53];

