#### Sample Calculation

We will consider a bilateral significance level (1-alpha) of 95%, power (1-beta) with 80% probability of detection, sample size ratio between exposed/unexposed of 1, percentage of positive unexposed of 50%[13] and percentage of positive exposure of 80%, Odds Ratio: 4, risk/prevalence ratio of 1.6 and risk/prevalence difference of 30, the calculation generated through OpenEpi, version 3.01, calculated 45 participants in each group (CG and IG) for UC patients, with a sample size of 90.

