#### Statiscal Analysis

Quantitative variables (age, disease duration, UC severity score, for example) will be described as means (standard deviation) or medians (interquartile range), while qualitative variables (gender, marital status, education, for example) will be described with absolute and percentage frequency measures. To compare exposed (GI) and non- exposed (CG) groups in relation to qualitative variables, the chi-square test or Fisher's exact test will be used, when recommended. The comparison of quantitative variables between exposure groups will be performed by applying Student's t test for unpaired samples or, if indicated, the nonparametric Mann-Whitney test.

The occurrence (incidence) of the study outcomes (non-adherence) will be performed by the ratio between the total number of participants who did not adhere to the treatment and the total number of participants in the group, multiplied by 100, calculated separately for the intervention and comparative groups. The relative risk (RR) with the respective 95% confidence interval (95%CI) will be used as a measure of efficacy, obtained by the ratio between the incidence of the intervention group and the incidence of the comparative group. For adjustments for potential confounders, Poisson regression with robust variance will be used to estimate adjusted RR with the respective 95%CI. Associations with p values lower than 0.05 will be considered significant.

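### On both Lichtiger forms a total of exactly 4 belongs to no disease-activity class, so the three-level status is undefined for patients with that score

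*Protocol*

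**What the plan says.** Appendix 3 (Time 0) and Appendix 4 (6 months) carry the same Lichtiger block. The interviewer circles one score for each of eight symptoms and enters the total ("Scores sum from the previous table"). The next instruction is "Classify clinical activity according to total score". Three classes follow: remission for totals below 4, "Light/moderate activity (5-10" and "Severe colitis (>10". The only remaining code is 9, not applicable.

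The Data Categorization section lists the index as the clinical variable: "disease activity - Lichtiger index[9], which establishes the clinical status of UC. This variable will be collected at Time 0 and 6 months".

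The statistical analysis section gives as examples "Quantitative variables (age, disease duration, UC severity score, for example", and provides for quantitative variables to be compared between groups by t test or Mann-Whitney test. It defines incidence and relative risk for non-adherence only.

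**The concern.** A classification rule should place every attainable value in exactly one class. This one skips a value, at the boundary that separates remission from activity. The skipped value is not exotic: good general well-being (2), light abdominal pain (1) and visible blood in fewer than half of movements (1), with every other item at 0, add up to 4.

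An interviewer who follows the form has no correct answer for such a patient. One may code NA, another may choose remission, a third the middle class, and the same patient may be treated differently at the two visits. Any table or covariate built on the recorded class would then contain avoidable missing values, or changes of status that come from the form and not from the disease. Duplicate data entry does not help, because both entries would copy the same arbitrary answer.

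**Working it through.** **Inputs.** Item maxima as printed in the Lichtiger table of Appendices 3 and 4: diarrhea 4, nocturnal diarrhea 1, visible bleeding 3, fecal incontinence 1, abdominal pain 3, general well-being 5, abdominal tenderness 3, antidiarrheal drugs 1. Class limits from the same forms: below 4, 5 to 10, above 10.

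**Step 1: range of the total.** 4 + 1 + 3 + 1 + 3 + 5 + 3 + 1 = 21. All item scores are whole numbers starting at 0, so the total takes the 22 values 0, 1, ..., 21.

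**Step 2: apply the printed classes.**

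| Total | Class as printed |
| --- | --- |
| 0 to 3 | remission |
| 4 | none |
| 5 to 10 | light/moderate |
| 11 to 21 | severe |

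The classes cover 4 + 6 + 11 = 21 of the 22 values. No value falls in two classes, and 4 is the only one in none. The result is the same on both forms.

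**Step 3: is 4 attainable?** The items allow 5 × 2 × 4 × 2 × 4 × 6 × 4 × 2 = 15,360 combinations of scores. Of these, 222 add up to 4. This shows only that the value can occur; it is not a patient frequency, and the protocol gives no distribution of the score.

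**Step 4: does either neighbouring assignment close the gap?** With remission at 4 or below, or with light/moderate running from 4 to 10, every total from 0 to 21 falls in exactly one class. The documents do not say which is meant.

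**Step 5: what depends on the class?** The sum is recorded before the class, so it does not depend on the class. The sample size rests on 50% versus 80%, two-sided alpha 0.05 and 80% power. With a continuity correction this reproduces the stated 45 per group, and no Lichtiger quantity enters it. Non-adherence is measured by the Morisky-Green-Levine test, which is separate.

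**Step 6: the bleeding item.** Its options are 0, under 50, over 50 and 100 percent, scored 0 to 3, so exactly 50% has no score. The choice is between 1 and 2, so the total can move by at most one point. Unlike the class gap, this one sits before the sum and cannot be undone from the sum.

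**The case against.** The best defence is that little is lost. Both forms keep the total, and the statistical analysis section already treats the severity score as quantitative. A patient with a total of 4 enters that comparison with the value 4 and can be given a class later by one line of recoding. This stands, and it limits the point to the categorical status.

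A reader might go further and infer that these patients drop out of the 6-month comparison of disease activity. The documents do not support that, for the reason just given.

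A reader might also infer a sizeable distortion of remission rates. If 5% to 15% of 90 participants scored 4, that would be 4.5 to 13.5 patients per visit. Moving 2 to 7 of 45 in one arm across the boundary would shift that arm's proportion by 2/45 = 4.4 to 7/45 = 15.6 percentage points. But the frequency is pure assumption, the protocol names no remission proportion as an outcome, and all such patients in the arm would have to be moved the same way. A bias between arms would further require the arms to be classed differently, while the section on participants' allocation states that outcome assessors are blind. Non-differential noise is the likelier result.

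It can also be said that a sign was lost when the PDF was read, since at-or-below 4 would close the gap. The top diarrhea option, printed as a bare 10, makes that possible. It cannot be excluded for the class limit or for the bleeding item. Both forms nevertheless read the same way, and nothing else in the protocol gives another reading.

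Leaving the matter to the statistical analysis plan, which is not shown, does not answer the point. This is a rule already printed on the data-collection forms.

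**Conclusion.** The point holds as a defect of the classification and no more. As printed, the three-level disease status is undefined for a total of exactly 4, at both visits, although the protocol relies on the index as the measure "which establishes the clinical status of UC". Its size is one of 22 possible totals; how many patients that means is unknown. The recorded sum and its quantitative comparison are not affected by the class gap, nor are the primary outcome and the sample size. The gap at 50% bleeding is real on the printed form but minor.

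This rests on two readings: that the signs in the text match the original forms, and that the severity score named in the analysis section is the Lichtiger sum. One might suppose that the cited index publication settles the class of a 4, but nothing in the protocol shows that it does.

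**What to change.** 1. Compare both forms with their originals for a lost sign at the remission limit and in the bleeding item.
2. If the gap is confirmed, reconcile the class limits so that every total from 0 to 21 falls in exactly one class, identically in Appendices 3 and 4. Where 4 belongs is the sponsor's decision; it should be documented before any group-level data are seen.
3. In the same edit, give exactly 50% bleeding a defined option.
4. Derive the class in the database from the recorded sum at both visits, overwriting the interviewer's entry.
5. Keep the 0 to 21 sum as the basis of the between-group comparison of disease activity, with the classes as description.

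The cost is an edit to two forms and one derived variable, with no extra patients or visits. If forms are already in use, step 4 still gives consistent classes from the totals on file. Bleeding answers already given at exactly 50% cannot be recovered from the sum.

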#### Appendice 5 – Registration of the Intervention Program

1. Código de identificação do participante: | | | | |

### Instructions: record the date and mark with an “X” the intervention(s) performed:

| DATE | INTERVENTION PROGRAME | | | | | | | |
| --- | --- | --- | --- | --- | --- | --- | --- | --- |
|  | EDUCATIONAL INTERVENTIONS | | | | BEHAVIORAL INTERVENTIONS | | | |
|  | Video playback about IBD | Delivery of the UC brochure | Guidance on prescribed drugs for UC | Other guidance (on demand) | Delivery of Therapeutic Scheme | Delivery of the Pharmaceutical Guidance Table | Sending SMS Reminder Type | Sending SMS Motivationsl Type |
|  |  |  |  |  |  |  |  |  |
|  |  |  |  |  |  |  |  |  |
|  |  |  |  |  |  |  |  |  |
|  |  |  |  |  |  |  |  |  |
|  |  |  |  |  |  |  |  |  |
|  |  |  |  |  |  |  |  |  |
|  |  |  |  |  |  |  |  |  |
|  |  |  |  |  |  |  |  |  |
|  |  |  |  |  |  |  |  |  |
|  |  |  |  |  |  |  |  |  |
|  |  |  |  |  |  |  |  |  |
|  |  |  |  |  |  |  |  |  |

Observations:

#### Appendice 6 – Video Development Roadmap

1. – Information on IBD – definition; Signs and symptoms; phases (acute and remission); systemic commitment; fistulas;
2. – General information about the treatment – drug and non-drug;
3. – Adherence information – need to adhere to treatment even when symptoms are absent; importance of adherence to the prescribed therapeutic regimen; expected results with treatment adherence (improvement in signs/symptoms, improvement in quality of life).

#### Appendice 7 - Text for Video Preparation

Hi! Welcome!

I'm [name], a member of the Research Group at the Center for Gastroenterology at the Federal University of Bahia.

This video aims to inform about the main inflammatory bowel diseases, providing general guidelines on the importance of adherence to treatment.

Inflammatory Bowel Diseases are chronic inflammatory diseases of the digestive system, which can start from the mouth and continue through the esophagus, stomach, intestines and rectum, ending in the anus. Our defense system, also called the immune system, attacks the digestive system, resulting in inflammation and other consequences. There are 2 most well-known types of Inflammatory Bowel Diseases: Crohn's Disease and Ulcerative Colitis.

In Crohn's Disease, any part of the digestive system can become sick, from the mouth to the anus. This disease is characterized by inflammation, and there may be a narrowing of some portion of the intestine, which makes it difficult for the food bolus or feces to pass. In addition, in some cases, it can cause what we call a fistula. A fistula is an opening that occurs between two organs that would not normally be communicating, and this increases the risk of infection.

In ulcerative colitis, the inflammation is limited to the large intestine.

The main symptoms of Inflammatory Bowel Diseases in general are diarrhea, abdominal pain, weight loss, blood and mucus in the stool and fever. However, symptoms outside the intestine can occur, such as joint pain, skin, and eye problems.

It is important to say that these diseases have a characteristic of entering the acute phase of crises where the discomforts are present and also in the control phase, which we call remission, where the symptoms are absent or very mild. The treatment does not only consist of the use of medication, but other factors are also important, such as a healthy diet, physical activity, when released, and stress management. Often, those who have Inflammatory Bowel Diseases, when they enter the remission phase, that is, control, have so much improvement that they believe they are cured, however, as the disease is chronic, if you discontinue the medication and all other measures, you can return to have crises.

The objective of treatment is to keep the disease under control, but, in addition, often even with no symptoms, when tests are performed, inflammation is still present. This inflammation can be present without symptoms, so treatment should be continued to achieve healing.

As Inflammatory Bowel Diseases have no cure, but control, treatment must be done throughout life. Be sure to take your medicines and always take them at the indicated times, because the more correct the use, the better the result. Most drugs do not take effect immediately, so the importance of maintaining continuous use, because when you stop the drug, it is as if you are starting from scratch. In addition, it is important to say that only with treatment is it expected to have a favorable result. In addition, with proper treatment, it is expected to have a quality life, being able to return to routine activities.

So, take care of yourself, and any questions about the treatment, contact the team of health professionals to guide you. If you have any discomfort due to the use of your medications, talk to your doctor or pharmacist.

We hope this video has helped you understand a little more about Inflammatory Bowel Diseases, and the importance of treatment. You can access this video at any time, as it is freely accessible to all.

Until later!

## Appendice 8 – Educational Brochure (Front and Back)

#### Appendice 9 – Roadmap for Preparing the Educational Brochure

- 1. – RCU information – definition; Signs and symptoms; phases (acute and remission); systemic commitment;
  2. – General information about the treatment – drug and non-drug;
  3. – Adherence information – need to adhere to treatment even when symptoms are absent; importance of adherence to the prescribed therapeutic regimen; expected results with treatment adherence (improvement in signs/symptoms, improvement in quality of life).

#### Appendice 10 - Medicines for UC available at FIMAE

| **MEDICATION / DOSAGE** | **PHARMACEUTICAL FORM / PRESENTATION** | **ADMINISTRATION ROUTE** |
| --- | --- | --- |
| Azathioprine 50mg | Pill | Oral |
| Cyclosporina 25mg | Capsule | Oral |
| Cyclosporina 50mg | Capsule | Oral |
| Cyclosporina 100mg | Capsule | Oral |
| Cyclosporina 100mg/mL | Oral suspension | Oral |
| Mesalamine 250mg | Suppository | Rectal |
| Mesalamine 400mg | Pill | Oral |
| Mesalamine 500mg | Pill | Oral |
| Mesalamine 800mg | Pill | Oral |
| Sulfassalazine 500mg | Pill | Oral |

**Appendice 11 – Roadmap for Guidance on Medicines**

1. Generic name of the drug (and trade name, if any), dosage, presentation, pharmaceutical form, route of administration;
2. Main contraindications, precautions and common adverse effects;
3. Most frequent drug interactions (drug/drug, drug/food, drug/alcohol and drug/smoking);
4. Storage, conservation and validity conditions according to the manufacturer;
5. Guidelines during use (examples: suppository application technique, use of the measuring cup).

**Appendice 12 – Model and Example of Therapeutic Scheme**

| [figure not shown]TIME | MEDICATION NAME | QUANTITY / PHARMACEUTICAL FORM | OBSERVATIONS FOR USE | | | OTHER OBS. |
| --- | --- | --- | --- | --- | --- | --- |
|  |  |  | FASTING  (1h ANTES) | DURING MEAL | 2h AFTER MEAL |  |
| 8:00 | Azathioprine 50mg | 1 pill |  |  |  | Daily use |
| 8:00 | Mesalamine 250mg | 2 suppositories |  |  |  | Daily use, laying position |
| 20:00 | Mesalamine 250mg | 2 suppsitories |  |  |  | Daily use, laying position |
|  |  |  |  |  |  |  |
|  |  |  |  |  |  |  |
|  |  |  |  |  |  |  |
|  |  |  |  |  |  |  |
|  |  |  |  |  |  |  |
|  |  |  |  |  |  |  |
|  |  |  |  |  |  |  |
|  |  |  |  |  |  |  |
|  |  |  |  |  |  |  |

## Appendice 13 – Reminder Text (SMS)

“Hello, remember that on / / at : hours your return to FIMAE is scheduled.”

#### Appendice 14 – Texts (SMS) of the Motivational Type

“Take care of your health”

“Remember to take your medication regularly”

